#### Clinicians

Potential participating clinicians must be employed by the PFCC at the Peter MacCallum Cancer Centre or the Royal Melbourne Hospital and involved in providing genetic counselling and testing to patients. Potential participating clinicians include associate and certified genetic counsellors, clinical geneticists, clinical genetic fellows, medical oncologists, and gastroenterologists.

### Recruitment

#### Patients

Recruitment will occur alongside standard PFCC clinical processes from May 2022 to December 2024, inclusive. Recruitment lists will be generated by reviewing the schedule for upcoming PFCC appointments and screening against the eligibility criteria. Eligible patients’ details including an email address will be entered into the study database hosted on REDCap at the Peter MacCallum Cancer Centre [26, 27]. The survey distribution tools in REDCap will be used to email study invitations. It is estimated based on the response rate of a similar genetic counselling intervention study that approximately 50% of invited patients will agree to participate [18]. Therefore, an estimated 702 potential participants will be invited to participate to achieve the requisite sample size.

The study database will house the Participant Information Statement, an e-consent framework, the GPRI, and all data collection instruments.

##### Randomisation

Randomisation of eligible patients to the intervention or control group will be conducted using randomly permuted blocks of varying sizes in a 1:1 ratio, stratified by sex and cancer status (affected or unaffected by cancer). The randomisation list will be computer-generated by an independent statistician and carried out centrally to ensure concealment. The study statistician will remain blinded until the database is cleaned, locked, and ready for unblinding. The statistical analysis plan will be written and published on our centre’s website while blind to group allocation. Blinding of patient and clinicians to the allocation status will not be possible because this is an open-label trial design.

#### Clinicians

All eligible PFCC staff will be invited to a short (30-min) study education session which will include training on how to use the GPRI. To participate in the study, clinicians agree to use the GPRI in appointments according to their clinical discretion with intervention group patients, and for all patients enrolled in the trial, audio-record the appointments and complete the post-appointment clinician checklist. Participating clinicians will also be invited to take part in a structured interview with a member of the research team.

### Data collection

#### Patient-administered measures

Participants will complete four questionnaires during the intervention phase (Fig. 1). After consenting, participants will complete the baseline questionnaire consisting of demographics and the GCOS-24. Two weeks after the first PFCC appointment, participants complete the second questionnaire including the GCOS-24 and the Genetic Counselling Satisfaction Scale (GCSS) [28]. Two weeks after the second PFCC appointment, participants complete the third questionnaire including the GCOS-24, the GCSS, the Multidimensional Impact of Cancer Risk Assessment (MICRA) [29], and the Psychological Adaptation Scale (PAS) [30]. Six months after the second PFCC appointment, participants complete the fourth questionnaire including the PAS, and purpose-designed items examining uptake of cancer risk management strategies and communication of genetic information to at-risk family members. For completion of each questionnaire, an email containing the relevant URL will be sent using the REDCAP automated survey invitation function that includes up to two reminders sent weekly to non-responders.

**Fig. 1 Fig1:**
[figure not shown]
Schedule of enrolment, interventions, and assessments for the POETIC trial. **−t1 PFCC appointment booked; t1 3 days prior to first PFCC appointment; t2 first PFCC appointment; t3 2 weeks after first PFCC appointment; t4 3 days prior to second PFCC appointment; t5 second PFCC appointment; t6 2 weeks after second PFCC appointment; t7 6 months after second PFCC appointment

#### Clinical data

Clinical data (e.g., genetic testing results, the number and type of referrals for psychosocial support, letters written for at-risk family members, referrals for risk management) will be collected at various time points during the study from Epic, an electronic health records system, used at the Peter MacCallum Cancer Centre and the Royal Melbourne Hospital.

#### Clinician data

##### Clinician checklist

After each appointment, clinicians will be asked to complete a checklist that is comprised of items that mirror the GPRI domains. Clinicians will complete this electronic case report form (eCRF) to report whether each psychosocial need was discussed (yes/no) or not applicable.

##### Structured interviews

Clinicians will be asked to complete a structured interview during the post-intervention phase of the study about their experiences of using the GPRI and the feasibility and sustainability of routine use after the conclusion of the trial. Interviews will be audio-recorded with verbal consent from the clinician at the beginning of the interview. The interviews will follow a structured guide comprising two sections: (1) demographics and (2) feasibility and sustainability of using the GRPI in routine practice. The demographics section will include profession, number of years practicing, and estimated number of times using the GPRI. Section 2 will include questions to explore: the clinician’s experiences of using the GPRI during appointments and whether they believe the GPRI to be a feasible and sustainable tool to use as part of routine care.

#### Healthcare resource use

A cost analysis comparing the intervention and control groups will be conducted from both a societal and public healthcare system perspective, using a bottom-up micro-costing approach. Clinicians will be asked to enter data pertaining to the time spent (in minutes) on administrative and clinical tasks for patients involved in the study. Clinicians will be asked to enter this data for 50 patients enrolled during the first 6–12 months of the intervention period and for 50 patients in the final 6–12 months. This will prevent over-burdening clinicians with data entry tasks and will allow analysis of the impact of gain of experience in using the GPRI.

#### Appointment data

Clinicians will be supplied with Dictaphones and asked to audio-record each appointment. Consent will be implied for clinicians through the opt in process and signing the delegation log and obtained from participants as part of their consent to take part in the overall study. At the end of each clinic, a member of the research team will collect the Dictaphones and transfer the audio recording onto the PFCC network drive. A member of the research team will listen to each appointment audio recording and, using a checklist, will record the frequency that psychosocial concerns included in the GPRI were discussed and whether psychosocial supports were offered. During the appointments where the GPRI was available, the audio recording will be reviewed to examine the adoption by clinicians of the GPRI during appointment, whether the GPRI was used as intended to assess fidelity, and the integration of the GPRI results in the appointment to examine penetration. The member of the research team involved in this aspect of study will not be associated with the clinician team to preserve clinician anonymity. The audio recordings will also be used to determine the length of each appointment.

#### Health economic data

Clinical data, patient-reported data, appointment data, and clinician data will be collated and used for the health economic analysis. Only costs directly related to the study intervention/genetic condition will be considered. The cost per patient will be established by (1) identification of relevant clinical pathways in consultation with study investigators, (2) estimate resource measurement for each pathway, (3) estimation of the unit cost for each resource, and lastly (4) application of the cost of resources to each clinical pathway. The cost of staff time will be based on time spent and the relevant gross salary award adjusted for on-costs (leave, leave-loading). Productivity costs (work absences, lost income) and out-of-pocket and indirect patient costs will be estimated using patient data collected through the clinical questionnaires.

## Data analysis

### Sample size

A total sample size of 246 participants, 123 per group, is required for 90% power to demonstrate that GPRI superior to usual care with a two-sided 5% significance level. This sample size is based on the following assumptions: a clinically meaningful absolute treatment difference in mean change in GCOS-24 scores from baseline to 2 weeks after the second PFCC appointment of 10 units in favour of GPRI (increase) [25], standard deviation (SD) of 20 units equal in each group, and at each time point (baseline, 2 weeks after first PFCC appointment, and 2 weeks after second PFCC appointment) [25], and conservatively no correlation between baseline and repeated measures of GCOS-24 scores. Attrition is estimated to be similar to another genetic counselling intervention study where approximately 30% participant attrition was observed [31].

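### The 702 planned invitations do not match the sample size of 246: the 30% attrition is already inside 246 and is applied a second time in reaching 702

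*Protocol article*

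**What the plan says.** The Sample size section (under Data analysis) states: "A total sample size of 246 participants, 123 per group, is required for 90% power to demonstrate that GPRI superior to usual care". The test is two-sided at α = 0.05. The section's assumptions are a 10-unit between-group difference in mean GCOS-24 change, an SD of 20 in each group at every time point, and no correlation between baseline and later scores. It then takes attrition from another genetic counselling study in which "approximately 30% participant attrition was observed". It does not say whether 246 is counted before or after that attrition.

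The Recruitment section (Patients) assumes that "approximately 50% of invited patients will agree to participate" and concludes: "Therefore, an estimated 702 potential participants will be invited to participate to achieve the requisite sample size". Uptake is the only factor it names between the invitation count and the sample size.

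The Statistical analysis section (Primary outcome) specifies a constrained longitudinal data analysis (cLDA) with a common baseline mean across groups. The Randomisation section gives 1:1 allocation.

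**The concern.** Half of 702 is 351, not 246. The only sample size the protocol states is 246, and no section gives 351 or explains the difference. The ratio 246/351 is 0.70, the retention that goes with 30% attrition. This suggests that 246 was treated as an evaluable number when the invitations were planned, although the Sample size section may already have inflated it for attrition.

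What is at stake is how the recruitment figures are read. Someone working from the invitation plan would expect about 351 enrolled. Someone working from the sample-size statement would expect 246. Each additional participant brings questionnaires, recorded appointments and clinician checklists.

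**Working it through.** **Inputs.** From Sample size: difference δ = 10, SD σ = 20, correlation 0, two-sided α = 0.05, power 90%, attrition 30%. From Recruitment: uptake 50%, invitations 702. From Statistical analysis: cLDA with a common baseline mean. Under that constraint and at zero correlation, baseline carries no information about follow-up, so the SD that matters is the follow-up SD of 20.

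**Step 1: reproduce 246.**
- Normal approximation: n per arm = 2(z₀.₉₇₅ + z₀.₉₀)²σ²/δ² = 2 × (1.960 + 1.2816)² × 400/100 = 84.06, so 85.
- The t-based minimum is 86 per arm (power 90.3%).
- Inflation for attrition: 86/0.70 = 122.86, so 123 per arm and 246 in total. This is the stated figure exactly. The normal version gives 85/0.70 = 121.4, so 122 per arm and 244 in total.

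**Step 2: alternatives that do not give 246.**
- No inflation: 170 (normal) or 172 (t).
- Multiplying by 1.30 instead of dividing by 0.70: 222 or 224.
- Raw change score, SD = 20√2 = 28.28: 338 or 340 uninflated, 484 or 486 inflated.

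Of the variants tried, only SD 20 with division by 0.70 leads to 246. On the stated inputs, 246 is therefore the number randomised.

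**Step 3: the invitation chain.**
- Forward from 702: 702 × 0.50 = 351 enrolled; 351 × 0.70 = 245.7 evaluable.
- Backward from 246: 246/0.70 = 351.4, taken as 351; 351/0.50 = 702.
- With attrition counted once: 246/0.50 = 492 invitations.
- Differences: 702 − 492 = 210 invitations; 351 − 246 = 105 participants, or 105/246 = 43%.

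**Step 4: power after 30% attrition (δ = 10, σ = 20).**

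| Randomised | Evaluable per arm | Power (t) | Power (normal) |
|---|---|---|---|
| 246 | 86.1 | 90.4% | 90.7% |
| 351 | 122.85 | 97.4% | 97.5% |

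**Step 5: could 246 be the evaluable number at 90% power?** With 123 evaluable per arm, power is 97.4% at SD 20 and 78.9% at SD 28.28. To get 90% exactly, the SD would have to be 10 × √(123/2)/(1.960 + 1.2816) = 24.2. For a change score this means a correlation of 1 − 24.2²/(2 × 20²) ≈ 0.27. The protocol states neither value, and it assumes a correlation of zero.

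**The case against.** The strongest defence is that 702 is only an estimate of how many people to invite. It is not a randomisation target: the protocol states one sample size, 246, and never mentions 351. If uptake is as expected, invitations can end early. This stands to the extent that 351 is an inference. It does not reconcile the figures, because 702 is presented as what follows from 50% uptake, and 50% uptake of 702 is not 246.

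A second defence is that the larger figure allows for patients who become ineligible when they do not consent to testing at the first appointment (Eligibility). Such losses are plausible, and exactly 492 invitations might not suffice. But the protocol gives no rate for them and does not link them to 702, while its own two percentages reproduce 702 to rounding.

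A reader might go further and infer that the trial is underpowered, or that the sentence giving 246 for 90% power is wrong. The documents do not support either. That sentence is correct if 246 is the number randomised, and enrolling more than 246 only raises power. Nor does the Sample size section contain a stopping rule that a larger enrolment would breach.

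**Conclusion.** The point holds as an inconsistency between two printed planning figures. The number out of line is 702; 246 reproduces exactly as the number randomised with 30% attrition included. Attrition enters a second time in the invitation estimate, which is about 210 higher than the stated uptake requires and implies about 105 more participants than the stated sample size.

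Power is at least 90% under both totals, and type I error and the primary analysis are unaffected. A claim that the plan sets two competing enrolment targets would go too far, since only 246 is stated. The defect is that 246 is not labelled as before or after attrition, and the invitation figure treats it as after.

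This rests on the stated inputs, on the cLDA making SD 20 the relevant one at zero correlation, and on participants lost to attrition contributing nothing at the primary time point. The calculation includes no allowance for clustering by clinician, which is a separate matter. Severity: should be fixed; not critical.

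**What to change.** In Sample size, state that 246 (123 per arm) is the number randomised, including 30% attrition, and that about 172 evaluable participants (86 per arm) give 90% power. In Recruitment, change 702 to about 492. If an allowance for patients who become ineligible by declining testing is wanted, add it with its assumed rate.

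Alternatively, if 351 randomised (246 evaluable) is what the investigators intend, say so in both sections and either restate the power as about 97% or give the assumptions under which 246 evaluable yield 90%.

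Either route costs a change to two sentences and to any matching ethics or registry entry. The first needs no additional participants and no change to design or analysis.

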### Statistical analysis

The biostatistician will devise a formal detailed statistical analysis plan for the study prior to unblinding. The analysis set will consist of all participants who were randomised, with all participants reported and analysed according to their randomised study arm. There is no interim-analysis planned due to the low risk of harm to participants presented by this trial.

#### Primary outcome

Primary outcome GCOS-24 scores will be analysed using a constrained longitudinal data analysis (cLDA) [32] model assuming a common mean across groups at baseline and a different mean for each group at each follow-up time point. The response will consist of all GCOS-24 scores (scores at baseline, and at 2 weeks after the first PFCC appointment and 2 weeks after the second PFCC appointment) and the model will include a random intercept for clinician and an unstructured variance-covariance matrix for the individual’s repeated measurements, factors representing treatment, time (categorical), and treatment-by-time interaction, and the stratification factors sex and cancer status at baseline, and will be further adjusted for cancer type. The mean change in GCOS-24 scores from baseline to each follow-up time point between the intervention group compared to the control group will be obtained. The primary hypothesis will be evaluated by obtaining the estimated difference between intervention and control groups in mean change in GCOS-24 score from baseline to 2 weeks after the second PFCC appointment, a two-sided 95% confidence interval and a *p*-value. This model provides valid inference in the presence of missing data if the data are missing at random. An analysis will be conducted using the delta-adjustment method under the pattern-mixture modelling framework in the context of multiple imputation to assess sensitivity to missingness not at random.

#### Secondary outcomes

In addition to the primary analysis of the GCOS-24 score, responders (defined as change from baseline to 2 weeks after second PFCC appointment in GCOS score ≥ 10) will be analysed using a logistic regression model using generalized estimating equations (GEEs) with an exchangeable correlation structure and robust standard errors for clustering by clinicians [33]. Continuous secondary outcomes with repeated measures—satisfaction with genetic counselling and adaptation to genetic risk—will be analysed using a linear mixed-effects model. The model will include a random intercept for clinician and an unstructured variance-covariance matrix for the individual’s repeated measurements and factors representing treatment, time (categorical), and treatment-by-time interaction. Other secondary outcomes, impact of genetic test result, and duration of PFCC appointments will be analysed using linear regression, total number of psychosocial needs identified in each appointment will be analysed using Poisson regression, and support offered to patients after appointments will be analysed using logistic regression. All these models will be fitted using GEEs with an exchangeable correlation structure and robust standard errors for clustering by clinicians and will be adjusted for the stratification factors sex and cancer status, with further adjustment for cancer type. These models provide valid inference in the presence of missing data if the data are missing completely at random (MCAR). Sensitivity analyses will be conducted using multiple imputation to explore the impact of any deviations from MCAR on the results.

Subgroup analyses for the comparison of the primary outcome, patient empowerment measured using the GCOS-24 score, for participants in the intervention group compared to the control group will be conducted by the stratification factors sex, cancer status (affected vs unaffected), and additionally by type of clinician (genetic counsellors vs doctors), including subgroup and an interaction term between treatment and subgroup in the model. All analyses of secondary outcomes and subgroups are exploratory and therefore require no adjustment for multiple testing. All statistical analyses will be conducted using Stata statistical software [34].

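### As written, the mixed model for satisfaction and adaptation leaves out the stratification factors and cancer type, which makes its standard errors modestly too large if the strata are prognostic

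*Protocol article*

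**What the plan says.** All references are to the protocol article.

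- **Randomisation:** allocation is 1:1 in permuted blocks, "stratified by sex and cancer status (affected or unaffected by cancer").
- **Statistical analysis, Primary outcome:** the constrained longitudinal model for GCOS-24 includes sex and cancer status and is further adjusted for cancer type.
- **Statistical analysis, Secondary outcomes:** satisfaction and adaptation "will be analysed using a linear mixed-effects model. The model will include a random intercept for clinician". The description continues with an unstructured covariance for the repeated measurements and three fixed terms: treatment, categorical time and their interaction. No stratification factor and no cancer type is listed.
- **Same section, further on:** the impact of the test result, appointment duration, number of psychosocial needs and support offered get regression models. The next sentence says that these models are fitted by GEE with robust standard errors for clinician clustering and "will be adjusted for the stratification factors sex and cancer status, with further adjustment for cancer type".
- **Same section, at the end:** all secondary and subgroup analyses are called exploratory.

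The opening of Statistical analysis promises a detailed analysis plan before unblinding. That plan is not at hand.

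**The concern.** The fixed effects of the mixed model are written out as a complete list. Sex and cancer status are missing from it, although they were used to balance the arms and appear in the primary model, which has nearly the same form.

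Stratified randomisation removes most of the chance imbalance in the strata, so the treatment estimate varies less from trial to trial. A linear model that omits the strata does not know this. It leaves the between-strata variance in the residual and reports a standard error larger than the true one. Confidence intervals are then too wide, type I error falls below its nominal level, and some power is lost on satisfaction and adaptation. Robust standard errors are specified only for the GEE models.

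**Working it through.** **1. The plan's own figure.** The inputs under Sample size are a "two-sided 5% significance level"; a sample that "is required for 90% power"; a difference "of 10 units in favour of GPRI (increase"); "standard deviation (SD) of 20 units equal in each group"; and 30% attrition.

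- Normal approximation: n per group = 2 × (1.960 + 1.282)² × (20/10)² = 84.1, so 85. The exact t calculation gives 86.
- With attrition: 86 / 0.70 = 122.9, so 123 per group and 246 in total. This matches "A total sample size of 246 participants, 123 per group".

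That number rests on the primary outcome, so nothing below changes it.

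**2. What each model adjusts for, as written.**

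| Model | Sex and cancer status | Cancer type |
|---|---|---|
| Primary GCOS-24 model | yes | yes |
| GCSS and PAS mixed model | not listed | not listed |
| GEE models for impact of result, duration, needs, support | yes | yes |
| GEE model for GCOS-24 responders | unclear: described before the adjustment sentence | unclear |

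**3. Size of the effect, by formula.** Let R² be the share of outcome variance explained by the strata. With balanced strata, the unadjusted model SE divided by the adjusted SE is 1/√(1 − R²). The article gives no R² for GCSS or PAS, so a range is assumed.

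| Assumed R² | Adjusted/unadjusted SE, √(1 − R²) | Unadjusted SE too large by | Type I error, unadjusted | Power after adjustment if 80% without |
|---|---|---|---|---|
| 0.02 | 0.990 | 1.0% | 0.048 | 80.8% |
| 0.05 | 0.975 | 2.6% | 0.044 | 82.0% |
| 0.10 | 0.949 | 5.4% | 0.039 | 84.0% |
| 0.20 | 0.894 | 11.8% | 0.028 | 87.9% |

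The last row shows the trend; nothing in the article suggests strata that strong.

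**4. Simulation with attrition.** The set-up was 246 randomised participants, stratified permuted blocks, one follow-up time point, a linear model, outcome SD 1 and 5,000 replicates. Block sizes of 4 and 6, 25% in the smaller sex group and 50% affected by cancer are assumptions. As a check, √(4/246) = 0.1275 without dropout and √(4/172) = 0.1525 with 30% dropout; the simulated unadjusted model SEs agree.

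| Strata R² | Dropout | Unadjusted: model SE / true SE | Type I error | With strata: model SE / true SE |
|---|---|---|---|---|
| 0.02 | 30% | 0.152 / 0.154 | 0.053 | 0.151 / 0.153 |
| 0.05 | 30% | 0.152 / 0.151 | 0.049 | 0.149 / 0.150 |
| 0.10 | 0% | 0.127 / 0.121 | 0.041 | 0.121 / 0.121 |
| 0.10 | 30% | 0.152 / 0.148 | 0.045 | 0.145 / 0.145 |

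At R² = 0.10 the mismatch falls from 5.6% without dropout (0.1274/0.1207) to 2.7% with 30% dropout (0.1523/0.1483), because dropout brings back some imbalance in the strata. At R² of 0.02 to 0.05 with dropout, no mismatch stands out from simulation error. With the strata in the model, model and true SE agree to within simulation error.

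**5. Baseline GCOS-24.** It was not a stratification factor, so omitting it creates no mismatch. Adding it to the strata-adjusted model (30% dropout) takes the model SE from 0.145 to 0.138 if it correlates 0.3 with the outcome, and to 0.124 at 0.5 (both with strata R² = 0.10). At zero correlation (strata R² = 0.02) it gains nothing: 0.151 against 0.152.

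Steps 3 to 5 approximate the stated model. They use one time point and no clinician effect.

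**The case against.** The best defence is that this is loose drafting in a condensed article. A detailed analysis plan is to follow, the adjustment policy is stated twice, and nothing says that the satisfaction and adaptation models are deliberately unadjusted. The article may simply mean the policy to cover every model.

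Part of this stands, and it limits the weight of the point. It does not remove it. The article fixes the random effect, the covariance and the fixed effects of this model, so the list reads as closed. The adjustment sentence describes GEE fitting, which is not how a mixed model with a clinician random intercept is fitted. Stretching the sentence to cover it would give the same outcomes two different estimators. Either way the wording needs correcting.

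Two stronger readings are tempting, and neither is supported.

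- **That omitting baseline GCOS-24 is an error too.** GCSS and PAS have no baseline of their own, and baseline GCOS-24 is collected in both arms, so a reader might infer this. But it measures empowerment, which is neither of these outcomes, and the article gives no correlation with them. In the primary model it is part of the response and not a covariate. Someone who adds an assumed correlation of 0.3 to 0.5 to a strata R² of 0.05 to 0.10 would claim a 7% to 19% smaller SE (√0.86 = 0.927; √0.65 = 0.806). Most of that comes from the assumed correlation.
- **That the mixed model departs from every other model in the plan.** The responder model comes before the adjustment sentence and has no adjustment statement of its own, so this cannot be said with confidence.

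**Conclusion.** The point holds as a modest, easily corrected weakness. As written, the GCSS and PAS mixed model omits the two stratification factors and cancer type, although the primary model includes all three.

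The unadjusted standard error exceeds the adjusted one by about 1% to 5% for an assumed strata R² of 0.02 to 0.10. A comparison with 80% power unadjusted would have about 81% to 84% with the strata included. At the planned 30% attrition, the gap between reported and true standard error is smaller still, and it is not visible at the low end of the range. If the strata do not predict satisfaction or adaptation, there is no loss.

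The treatment estimates remain unbiased and any error is conservative. The outcomes are exploratory, and the primary conclusion and the 246 participants are unaffected. The direction of the effect follows from the design; its size rests on an R² that the article does not give.

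**What to change.** State in the analysis plan, before unblinding, that the mixed models for GCSS and PAS also adjust for sex, cancer status and cancer type, coded as in the primary model. The same edit could name each model that the adjustment covers, which would settle the responder model as well.

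Optionally, prespecify baseline GCOS-24 as a further covariate in the GCSS and PAS models for possible extra precision. This is a choice for the trial statistician and does not correct a fault.

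The core change costs one sentence. It needs no new data, since the primary model already uses all three variables, and no change to the sample size. Fixing it now also avoids choosing covariates once the allocation is known.

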#### Secondary outcomes

The effectiveness of using the GPRI, relative to usual care, will be further explored through secondary outcomes including change in GCOS-24 score from baseline to 2 weeks after the first PFCC appointment and proportion of respondents who meet the Minimum Clinically Important Difference (MCID) whose GCOS-24 score changes ≥10 points from baseline to 2 weeks after the second PFCC appointment [25]. Other secondary outcomes include patient satisfaction at 2 weeks after first and second PFCC appointments, patient adaptation 2 weeks and 6 months after the second PFCC appointment, and impact of genetic test result 2 weeks after the second PFCC appointment. Uptake of cancer risk management strategies and communication of genetic information to at-risk family members will be assessed at 6 months after the second PFCC appointment. The proportion of psychosocial needs identified by clinicians during the PFCC appointments, support offered after the PFCC appointments, and duration of the PFCC appointments will be established. Implementation outcomes including cost-effectiveness, adoption (uptake of the GPRI by clinicians during appointments), fidelity (use of GPRI and extent of use by clinicians during appointments), penetration (number of clinicians who use the GPRI during appointments), and clinicians’ perceptions of the feasibility and sustainability of using the GPRI routinely will also be assessed.

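### The exploratory MICRA model leaves out the genetic test result that the trial already collects, which may cost precision but not validity

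*Protocol article*

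**What the plan says.** All references are to the protocol article.

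- **Model.** Under Statistical analysis, Secondary outcomes: "Other secondary outcomes, impact of genetic test result, and duration of PFCC appointments will be analysed using linear regression". These models use GEE with an exchangeable correlation and robust standard errors for clinician clusters.
- **Covariates.** The same paragraph says that they "will be adjusted for the stratification factors sex and cancer status, with further adjustment for cancer type". The test result is not in this list. It is not a stratification factor under Randomisation, nor one of the subgroups.
- **Availability of the result.** Clinical data lists "genetic testing results, the number and type of referrals for psychosocial support" among the items drawn from the electronic health record.
- **Timing.** Setting says that the result is given at the second appointment. Table 1 and Patient-administered measures place MICRA once, two weeks after that appointment. There is no baseline MICRA.
- **Status.** All secondary analyses are called exploratory, and a detailed SAP is to be written before unblinding.

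**The concern.** MICRA is introduced as the impact of the genetic test result, so whether a pathogenic variant was found is a natural candidate predictor of the score. With no baseline measurement, the usual source of precision is absent. The authors already go beyond the stratification factors by adding cancer type, yet they leave out the one collected variable that the outcome is about.

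Germline status is set before randomisation and the GPRI cannot change it. Among those tested, adjusting for it in a linear model therefore does not remove part of the treatment effect. What is at stake is the width of the confidence interval for one exploratory outcome.

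**Working it through.** **1. The plan's own figure, to fix the number of completers.** The article plans for 246 in total, 123 in each arm, and says that this number "is required for 90% power to demonstrate that GPRI superior to usual care with a two-sided 5% significance level". Its inputs are a "mean change in GCOS-24 scores from baseline to 2 weeks after the second PFCC appointment of 10 units in favour of GPRI", a "standard deviation (SD) of 20 units equal in each group", zero correlation with baseline, and 30% attrition.

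- Per arm, normal approximation: 2 × (1.960 + 1.282)² × 20² / 10² = 84.1, so 85. With the t distribution it is 86.
- Inflated for attrition: 86 / 0.7 = 122.9, so 123 per arm and 246 in total. The stated figure reproduces and already includes attrition.
- Completers: 123 × 0.7 ≈ 86 per arm, 172 in total.

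This calculation is for GCOS-24. The article gives no SD, effect or power for MICRA.

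**2. Assumed inputs.** The article gives no carrier share p and no carrier/non-carrier gap d. I take p from 10% to 20% and d from 0.5 to 1.5, in units of the SD within result group.

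**3. Precision.** With v = p(1−p)d², the result explains R² = v/(1+v) of the variance. Adjustment cuts the standard error by 1 − √(1−R²).

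| p | d = 0.5 | d = 1 | d = 1.5 |
|---|---|---|---|
| 10% | R² 0.022, cut 1.1% | R² 0.083, cut 4.2% | R² 0.168, cut 8.8% |
| 15% | R² 0.031, cut 1.6% | R² 0.113, cut 5.8% | R² 0.223, cut 11.8% |
| 20% | R² 0.038, cut 1.9% | R² 0.138, cut 7.2% | R² 0.265, cut 14.3% |

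For the middle case, v = 0.15 × 0.85 × 1² = 0.1275, R² = 0.1275/1.1275 = 0.113, and 1 − √0.887 = 5.8%. The information given up equals 0.113 × 172 ≈ 19 participants. An effect that the adjusted model detects with 80% power is detected with about 75% power without the covariate.

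The formula treats the result as unrelated to sex, cancer status and cancer type. To the extent that these already predict it, the gain is smaller.

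**4. Chance imbalance.** At p = 15%, the difference in carrier share between arms has SD √(2 × 0.15 × 0.85 / 86) = 0.054, or 5.4 percentage points, with 95% limits of about ±10.7 points. At d = 1 this moves the unadjusted estimate by up to 0.107 SD. The adjusted standard error is √(2/86) = 0.152 SD, so the shift is up to 0.70 standard errors.

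**5. Validity of the stated model.** A simulation of 20,000 trials at p = 15%, d = 1 and 86 per arm, without clinician clustering, gave:

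- mean error 0.000 with and without the covariate;
- type I error 5.1% without it and 5.2% with it;
- a ratio of standard errors of 1.06.

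The omission costs precision. It causes neither bias nor an inflated error rate.

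**The case against.** The strongest reply is that nothing here is wrong. The model compares randomised arms, adjusts for both stratification factors, and serves an exploratory outcome for which no power is claimed. An SAP is still to come and could add the covariate. The gain depends on two figures that the article does not give, and at a gap of 0.5 SD it is negligible. All of this stands and sets the weight of the point. It does not remove it, because the article states a covariate list for this outcome instead of leaving it open.

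The covariate is also less clean than germline status itself. A reported result exists only for those tested, and it depends on which test is ordered. Consent to testing is given at the first appointment, after open-label allocation, and patients who decline become ineligible. The models with and without the covariate share this selection, so comparing them does not test for it.

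A reader might infer more than the documents support:

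- **That carrier imbalance biases the MICRA comparison.** It does not. The imbalance is random error, and the confidence interval of the stated model already reflects it.
- **That the result is the main driver of MICRA.** Only the name and timing of the outcome suggest this. No figure in the article shows it.
- **That the same change is needed for adaptation, risk management and family communication.** Adaptation has a separate mixed model. For the other two the article says "Uptake of cancer risk management strategies and communication of genetic information to at-risk family members will be assessed at 6 months" but fixes no model, so there is no covariate list to criticise. Nor does it say that participants without a variant have nothing to communicate or act on, so dilution by them is not established.
- **That arms should be compared among carriers only.** At 10% to 20% of 86, that leaves about 9 to 17 people per arm, too few to be informative.

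**Conclusion.** The point holds as a minor matter of efficiency, confined to MICRA. The stated model is valid but omits a collected covariate that probably bears on the score and that the intervention cannot alter. For carrier shares of 10% to 20%, the standard error given up is about 1-2% at a gap of 0.5 SD, 4-7% at 1 SD and 9-14% at 1.5 SD. These sizes rest wholly on assumed carrier shares and gaps, on a two-category result, and on no overlap with the covariates already in the model. Overlap would make them smaller. The primary outcome and the sample size are not affected.

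**What to change.** In the SAP, before unblinding, add the test result (pathogenic variant found or not) to the covariates of the MICRA linear model. State in advance how uncertain results are classed. Report the model without the result as a sensitivity analysis.

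Report by arm the number tested and the distribution of results. This makes selection into testing after open-label allocation visible, although neither model removes it.

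The cost is one covariate and a few lines of reporting, with no new data collection. Specifying it now also avoids a choice made after any carrier imbalance has been seen.
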